##### Data collection

On the day of enrollment, all women will be interviewed using a pretested structured questionnaire to identify basic baseline characteristics. They will then be followed up via phone bi-monthly for 8 months to assess how the intervention influences dual-method use and pregnancy and STI incidence (2, 4, 6, and 8 months after enrollment). All interviews will be conducted by trained female research assistants using an interview guide in either English or Runyankore. All data will be entered using EpiData version 4.6.

All participants will be given some incentives worth 10,000 UGX (equivalent to US$3) for their time and participation in the study after the initial interviews. Participants who participate in the learning workshop will receive 20,000 UGX (equivalent to US$6) for transportation.

##### Data analysis

The background characteristics of women will be compared between the intervention and the control group using Pearson’s chi-squared or Fisher’s exact tests [44]. Mixed effects logistic regression analysis will be performed with a random effects term for the clusters to access the effect of the intervention on the following outcomes: dual-method selection and adherence; self-reporting pregnancy; and incidence of STI in the 2 months before each follow-up data collection. In addition, hierarchical logistic regression model will be introduced to ascertain the predictors of each outcome. Model 1 will be adjusted for demographic variables, such as age, education, and the number of children. Model 2 will be adjusted for the status of residence (urban or rural) in addition to demographic variables. Model 3 will include the type of HECs at the baseline sequentially, which is known to be associated with dual-method use [8, 45]. Model 4 will be adjusted for variables related to their partners, such as partner’s attitude toward family planning. Model 5 will include women’s perceived risk of HIV/STIs. Model 6 (full model) will be adjusted for all variables. Besides, sub-group analyses will be conducted among HIV-seroconcordant and -discordant couples. All the analyses will be conducted on both per-protocol and intention-to-treat bases. The per-protocol analysis will assess the efficacy of the intervention while the intention-to-treat analysis will test its effectiveness [46]. Rates of attrition and reasons for dropout will be compared between the intervention and the control groups [47]. The significance level will be set at 5%. STATA version 13.1 will be used for all data analyses.

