#### Phase I: identify positive deviants

##### Sample size, eligibility, and recruitment

In Phase I, 150 women will be interviewed. This is based on the assumption that at least 7% of women would practice dual-method use [13] and at least 10 women who are considered as a positive deviant would be identified.

To be eligible for joining this study, participants should have the following characteristics: (1) women; (2) aged 18–49 years; (3) sexually active; (4) using HECs at the time of recruitment; (5) have a desire to avoid pregnancy for 12 months from recruitment; (6) have a husband or live-in sexual partner; and (7) have access to a valid phone number.

Being sexually active is defined as having had sexual intercourse in the 3 months before the study [13]. Pregnant women and women who are infertile for other reasons will be excluded from this study. Health workers, including community health workers, political and religious leaders, and teachers will also be excluded because they may not represent communities or be influenced by their occupations and social status.

For sampling, five health facilities will be selected purposively. Then, five trained female research assistants will approach female clients in the family planning sections of the selected health facilities. The first client will be selected randomly at each clinic and then every third client will be informed about the opportunity to participate in this study. If they are interested in participating, the research assistants will ask screening questions using a pretested questionnaire to check their eligibility for the study. This process will be repeated until the required sample size is met.

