#### Phase II: cluster randomized controlled trial

##### Sample, eligibility, and recruitment

The minimum required sample size for this trial is 588. It was calculated based on data from research on the effect of case management and peer education program on the uptake of dual- method use in the USA (odds ratio [OR] = 1.58, 95% confidence interval [CI] = 1.03–2.43) [32]. The less conservative effect size of 2.43 was used because this trial will include only women who have already used HECs, unlike the prior research which recruited adolescent girls regardless of their contraceptive use [32]. Then, an intraclass correlation coefficient (ICC) of 0.006 was considered [33, 34]. The ICC was adapted from a clinic-based condom use intervention in SSA [33]. The required minimum sample size was 760 after considering the ICC. Considering a 26% dropout rate, 960 participants will be recruited (480 participants in each arm) [22]. The power of the study was set at 80% and the significance level was set at 5%. Open Epi version 3 was used for the calculation.

Twenty health facilities will be purposively selected considering the size and rural/urban status. The same inclusion criteria as Phase I will be used for this intervention study, but if women have been practicing dual-method use in the 2 months before recruitment, they will be excluded. The same sampling method as Phase I will be used to recruit women at health facilities. Eighty women will be recruited from each of the hospitals and county-level health centers, and 40 from each of the sub-county-level health centers and parish-level health centers.

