##### Outcomes

The primary outcome is dual-method use. In this study, dual-method use is defined as the use of male or female condoms along with HECs such as pills, injectables, implants, male and female sterilization, and IUD consistently in the last 2 months, before each follow-up interview [8]. The outcome measure combines two questions regarding the frequency of condom use and HEC use. The frequency of condom use will be asked with an item: “How often did you and your partner use a male or female condom during the past 2 months?” Women will answer this question using a four-point scale “every time,” “almost every time,” “sometimes,” and “never.” Only those who answered “every time” will be considered as having consistent condom use. Women will also be asked if they have been using any HECs with a question, “Apart from condoms, have you been using any other forms of protection against pregnancy during the past two months?” Responses to these two questions will be used to construct the dual-method use outcome with the following categories: (1) dual-method use (consistent condom and HEC use); (2) inconsistent use of condoms and HECs; and (3) single or no use of contraceptive methods.

The secondary outcome is the self-reported first occurrence of pregnancy and STIs in the previous 2 months [37]. They will be assessed with the following two questions: “Have you been told by a healthcare provider that you got pregnant for the first time in the past 2 months?” and “Have you been told by a healthcare provider that you had any STIs such as chlamydia, gonorrhea, or trichomonas infection for the first time in the past 2 months?”

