### Trial status

Enrollment into the trial is expected to start in October 2019 and end in November 2019. The trial is expected to be completed by June 2020. This manuscript was based on the study protocol version 8 and the version date is 5 August 2019.

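### The primary outcome is assessed at four follow-ups with no primary visit, overall contrast or analysis set named, and the stated model has a facility term but none for the woman

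*Protocol article*

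**What the plan says.** The Outcomes section of Phase II defines dual-method use as condom and highly effective contraceptive use "consistently in the last 2 months, before each follow-up interview". The Data collection section sets four interviews, at months 2, 4, 6 and 8: "They will then be followed up via phone bi-monthly for 8 months to assess how the intervention influences dual-method use".

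The Data analysis section gives the model: "Mixed effects logistic regression analysis will be performed with a random effects term for the clusters to access the effect of the intervention". It again ties the outcomes to the two months ahead of every follow-up, and one level serves everything: "The significance level will be set at 5" per cent. Six adjusted models for predictors follow. All analyses are to be run on both per-protocol and intention-to-treat bases, the first for efficacy and the second for effectiveness. Neither is called primary.

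The sample-size section works with one effect and one level: "The less conservative effect size of 2.43 was used", and "The power of the study was set at 80% and the significance level was set at 5" per cent. Its only correlation is a facility ICC of 0.006.

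**The concern.** Each woman can supply the primary outcome four times, and the plan does not say which answer, or which summary of the four, decides the trial. There are two ways to apply the stated model.

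- **Visit by visit.** There are up to four results for the primary outcome, each judged at 5%. A claim of success could rest on whichever visit is favourable, so the 5% error used to size the trial is not protected.
- **Pooled.** The one random effect described is for the facility. Repeated answers from a woman are then treated as independent once her facility is accounted for.

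The visits also ask different questions. The month-2 recall period starts at enrolment. It covers the enrolment-day counselling and, from two weeks on, the workshop, but none of the phone sessions at months 3, 5 and 7. Month 8 comes after every component. The text lets either be presented as the main result.

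**Working it through.** **1. The plan's own figure.** Inputs from the sample-size section: odds ratio 2.43, power 80%, level 5% (two-sided assumed). The control proportion for Phase II is not stated. The Phase I figure ("at least 7% of women would practice dual-method use") serves another purpose and does not reproduce 588. I assume 5%.

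- Intervention proportion: 0.05 × 2.43 / (1 + 0.05 × 1.43) = 0.1134. Mean of the two: 0.0817.
- Kelsey formula per arm: (1.960 + 0.842)² × 2 × 0.0817 × 0.9183 / 0.0634² ≈ 293.1, rounded up to 294. Total **588**, as stated.
- The same formula gives 500, 438 and 392 at control rates of 6%, 7% and 8%.
- Clustering: 1 + (50 − 1) × 0.006 = 1.294, and 588 × 1.294 = 760.9, against the stated **760**. The 50 per facility is inferred; 48 gives 753.8.
- Dropout: 760 × 1.26 = 957.6, close to the stated **960**.

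The whole chain is one comparison of two proportions. It contains no allowance for several visits and no within-woman correlation.

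**2. Four tests at 5%.** If independent: 1 − 0.95⁴ = 18.5%. Tests on the same women are correlated, and the documents give no correlation. Simulating four two-sided z statistics with equal correlation gives:

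| Assumed correlation between tests | At least one false positive |
|---|---|
| 0.3 | 17.4% |
| 0.5 | 15.6% |
| 0.7 | 13.1% |
| 0.9 | 9.4% |

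**3. Cost of keeping all four as primary.** With Bonferroni each test is at 0.05 / 4 = 0.0125. At 588 women and the assumed 5% control rate, power falls from 80% to about 62%. The size before clustering would be (2.498 + 0.842)² × 2 × 0.0817 × 0.9183 / 0.0634² ≈ 416.4, so 417 per arm and 834 in total. With the same design effect, 834 × 1.294 ≈ 1,079.

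**4. Pooled, woman-level predictors.** For a covariate that is constant within a woman, k visits with correlation ρ multiply the true variance by 1 + (k − 1)ρ relative to independence. With k = 4:

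| Assumed ρ | Variance ratio | SE too small by | Actual error of a nominal 5% test |
|---|---|---|---|
| 0.3 | 1.9 | 1.38 | 15.5% |
| 0.5 | 2.5 | 1.58 | 21.5% |
| 0.7 | 3.1 | 1.76 | 26.6% |

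This supposes all four visits complete. With three, the SE factor is √1.6 = 1.26 at ρ = 0.3 and √2.4 = 1.55 at ρ = 0.7.

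**5. Pooled, arm test.** Arm is assigned by facility, so the facility random effect takes up most of the within-woman correlation. Trials were simulated with 20 facilities, about 38 women each or 4 of 60 and 16 of 30, outcome prevalence 10%, in a linear approximation:

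| Latent within-woman correlation | Normal reference | t on 18 df |
|---|---|---|
| almost none (0.02) | 7.2% to 7.5% | 5.4% to 5.5% |
| 0.5 to 0.9 | 7.5% to 8.8% | 5.8% to 7.0% |

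A second simulation (1,200 trials per setting, Monte Carlo error about 0.7 points) compared the normal-reference test without and with within-woman correlation. The error went from 7.5% to 7.3% at a facility ICC of 0.02, and from 5.3% to 8.3% at 0.006. With t on 18 df the two correlated settings gave 5.4% and 6.6%.

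**6. Dates, a separate minor matter.** The Trial status section ends enrolment in November 2019 and says "The trial is expected to be completed by June 2020". November 2019 plus 8 months is July 2020.

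**The case against.** A reader might infer that the protocol plans four separate primary tests. It does not say so. The reference to each follow-up may only describe the recall window, and grammatically it may attach only to the last outcome listed. Separate testing is the natural reading, not a stated one. The gap remains under either reading, because no visit and no overall contrast is named.

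The article condenses a longer protocol, and a statistical analysis plan may exist. Naming a random effect for clusters does not exclude a second one for women, and that detail is commonly left to the analysis plan. This weakens the point about the woman-level term. It does not answer the point about the primary time point, which is part of the definition of the primary outcome.

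Four stronger readings go too far:

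- 18.5% as the expected error. It needs independent visits, which repeated answers from the same women are not.
- 16% to 27% as the error of the main comparison. Those figures concern Models 1 to 6, which the protocol introduces to look for predictors, and only if visits are pooled.
- Serious damage to the arm test from pooling. Much of the simulated excess appears with almost no within-woman correlation, and comes from a normal reference with 20 clusters.
- Month 2 as an unexposed visit. Enrolment counselling precedes it and the workshop falls inside its window.

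Nor does running both analysis sets simply double the tests, since the protocol gives each its own question. What stands is that neither is named as the primary one.

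**Conclusion.** The concern holds in this form: the plan sizes for one 5% test but does not identify that test among four visits and two analysis sets. If each visit is tested at 5%, the chance of at least one false positive is about 9% to 17% for assumed test correlations of 0.9 to 0.3. If visits are pooled with the facility term alone, the main harm is to woman-level predictors, with standard errors too small by about 1.4 to 1.8 at assumed within-woman correlations of 0.3 to 0.7 and complete follow-up. The effect on the arm test is modest and shared with the small number of clusters. None of these correlations is in the documents, and the power figures rest on the assumed 5% control rate. The missing primary contrast depends on none of these assumptions. It decides what the trial can claim, so it should be settled before outcome data are analysed. The completion date adds no weight to it.

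**What to change.** - Pre-specify one primary intention-to-treat arm contrast: either month 8, after all intervention components, or one overall contrast across visits. Either holds 5%.
- Take it from a mixed logistic model with visits within women within facilities, and terms for arm, visit and arm by visit.
- Use a small-sample, t-type reference for the arm test, because there are only 20 facilities.
- Report the remaining visits and the per-protocol analysis as secondary.
- Include the woman-level random effect in Models 1 to 6 wherever visits are pooled.
- Separately, reconcile the June 2020 completion date with enrolment to November 2019 plus 8 months of follow-up.

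The cost is a few sentences and slightly heavier model fitting, and the other visits lose confirmatory status. One named test leaves 588, 760 and 960 unchanged. The model also uses women with partial follow-up, which is useful given the attrition that the Discussion expects, especially in the control arm.

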##### Intervention

The intervention will consist of a series of counseling and participatory workshops, planned based on the unique practice identified in Phase I. On the day of enrollment, women in the intervention arm will receive dual-method counseling with a tool developed based on the practice identified in Phase I, in addition to regular family planning counseling with an existing counseling tool [36]. The dual-method counseling will be conducted for 20–40 min by trained research assistants.

Two weeks after enrollment, women in the intervention arm will be invited for a 1-day participatory learning workshop (5 h) at the same health facilities where they were recruited. Women may decide whether to participate. The workshop will be facilitated by research assistants and positive deviants, using a training protocol developed after Phase I. It will include simulations and role-plays for successful communication about using a condom with their partners and a group discussion regarding family planning and HIV/STI risk.

Bi-monthly telephone counseling will be provided by positive deviants three times (3, 5, and 7 months after enrollment). Each counseling session will take 10–20 min and aim to remind women of the risk of unintended pregnancies and HIV/STIs and strengthen their capacity to communicate using a condom with their partners. The 2-month intervals can allow women to reflect on counseling messages, discuss the use of condoms with their partners, and put it into practice. Positive deviants, therefore, can provide more effective counseling tailored to participants’ individual needs through understanding their situation.

Women in the control group will be provided regular family planning counseling including dual-method use for 10–30 min by trained research assistants using the same existing tool on the day of enrollment [36]. Moreover, refresher training will be provided bi-monthly on family planning and HIV/STI risk via phone, by research assistants three times (3, 5, and 7 months after the enrollment).

Condoms will be provided for free, regardless of the allocation at the selected health facilities. Before the intervention starts, the research assistants will receive a 2-day training session about the contents of the existing counseling tool by health professionals [36].

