The present study has several limitations. First, the success of the positive deviance approach depends on whether women practicing dual-method use or positive deviants can be found in the study area [24, 48]. Considering the prevalence of such people, the sample size can be too small and may need to be modified. Second, positive deviants are identified by the research team not by community members in this trial. Therefore, the effect of the intervention can be limited in mobilizing and empowering communities to adopt identified strategies, compared to the usual approach including self-discovery of positive deviants [24, 48]. Third, high attrition is anticipated, especially among women in the control arm, as all the interventions and follow-ups after recruitment and initial counseling are phone-based [11]. The present trial, therefore, calculated the sample size considering a relatively high attrition rate to offset potential losses to follow-up. Moreover, it will be minimized by building rapport with participants. For this, each participant will be contacted by the same positive deviant and/or research assistant for counseling and follow-up throughout the study period. Fourth, the outcomes will be assessed based on self-reports from participants and thus subject to response bias. Dual-method use can be over-reported while the incidence of STIs and unintended pregnancies can be under-reported due to social desirability bias. However, response bias will be minimized by assuring each participant of confidentiality of responses at the enrollment. Lastly, findings of the present study might lack external validity to other locations as it will focus on one particular community under the positive deviance approach [48]. In the present study, participants will be recruited in only public health facilities; thus, findings from this study may not be generalized to all women using HECs. To apply findings and the interventions developed in the present study to other areas and populations, further research will be necessary to assess its effectiveness in a given context.

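### Every analysis is run both per protocol and by intention to treat with neither primary, and an undefined per-protocol comparison is presented as the measure of efficacy

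*Protocol article*

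**What the plan says.** The Data analysis section for Phase II states: "All the analyses will be conducted on both per-protocol and intention-to-treat bases". It then divides the roles: "The per-protocol analysis will assess the efficacy of the intervention while the intention-to-treat analysis will test its effectiveness". One 5% significance level is given for all of this. The section neither says which basis is primary nor which governs if the two disagree. Objective 2 in Study objectives is to evaluate the effect of the intervention and does not say which of the two estimates answers it.

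The Intervention section gives the arms different contacts after allocation:

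- **Intervention arm:** 20–40 minutes of dual-method counselling at enrolment on top of regular counselling, a 5-hour workshop two weeks later, and three calls from positive deviants at 3, 5 and 7 months. On the workshop it says: "Women may decide whether to participate".
- **Control arm:** 10–30 minutes of regular counselling at enrolment and three refresher calls from research assistants in the same months. No workshop is described.

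Among its limitations, the Discussion says that "high attrition is anticipated, especially among women in the control arm".

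**The concern.** This is a superiority trial with facilities randomised. Randomisation protects only the comparison of all enrolled women by the arm of their facility. A per-protocol set defined by what women do after allocation gives up that protection unless adherence is unrelated to the outcome. Women who choose to spend five hours on condom negotiation plausibly differ in motivation and partner support from those who decline, and no control woman faces that choice.

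Two things are at stake. First, a selected comparison would be reported as the efficacy of the intervention. Second, because neither result is ranked, a reader cannot tell in advance which one decides objective 2 if they differ, and the authors could settle that after seeing the data.

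**Working it through.** **What the article fixes.** It gives no figure on this point, so there is none to reproduce. It fixes two bases for every analysis, one 5% level, no ranking, and efficacy as the role of per protocol. It gives no criterion for the per-protocol set.

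**Which definitions are plausible, and what each would do.**

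| Per-protocol set requires | Effect on the arms |
|---|---|
| Workshop attendance | Filters the intervention arm only |
| Counselling or calls completed | Same call months in both arms, but content, caller and burden differ |
| Follow-up completed | More loss is expected among controls, so the arms are filtered differently |

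All three condition on behaviour after randomisation. The first can be illustrated numerically.

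**Illustration with no true effect, per protocol meaning workshop attendance.** The inputs are:

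- Control uptake p_C = 7%. This is assumed: the article uses 7% for Phase I screening and states no Phase II control rate. The range 5% to 10% is also run.
- Attendance a = 40%, 60% or 80% (assumed).
- Ratio r of uptake in attenders to non-attenders, regardless of the workshop = 1.5, 2 or 3 (assumed).

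With no effect, the intervention arm as a whole also has uptake p_C. So non-attenders have p_N = p_C / (a·r + 1 − a), attenders have p_A = r·p_N, and the per-protocol odds ratio is [p_A/(1 − p_A)] / [p_C/(1 − p_C)].

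Worked case with a = 0.4 and r = 3: p_N = 0.07/(1.2 + 0.6) = 0.0389, p_A = 0.1167, and OR = 0.1321/0.0753 = 1.75.

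For the chance of a significant result, expected completers are 960 × 0.74 = 710.4, or about 355 per arm. Over 10 facilities that is about 36 each, so the design effect is 1 + 35 × 0.006 = 1.21, using the article's intraclass correlation. The comparison is 355·a attenders with 355 controls by a two-sided 5% z-test, with the standard error of the difference multiplied by √1.21. Results at p_C = 7%:

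| Attendance | r | Attender uptake | OR with no effect | Chance of a significant result |
|---|---|---|---|---|
| 40% | 1.5 | 8.75% | 1.27 | 9.0% |
| 40% | 2 | 10.0% | 1.48 | 15.9% |
| 40% | 3 | 11.67% | 1.75 | 29.1% |
| 60% | 1.5 | 8.08% | 1.17 | 7.1% |
| 60% | 2 | 8.75% | 1.27 | 10.3% |
| 60% | 3 | 9.55% | 1.40 | 15.9% |
| 80% | 1.5 | 7.5% | 1.08 | 5.6% |
| 80% | 2 | 7.78% | 1.12 | 6.3% |
| 80% | 3 | 8.08% | 1.17 | 7.5% |

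Over control rates of 5% to 10%, the odds ratio runs from 1.08 to 1.80 and the chance of a significant result from 5.4% to 40.8%. For scale, the cited US study reported an odds ratio of 1.58, and the trial is sized on 2.43.

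**Two unranked tests.** This part leaves selection aside and asks what happens if success could be claimed on either basis at 5%. For independent tests the false-positive chance is 1 − 0.95² = 9.75%. The two tests share most of their data, so they would be correlated. Simulation gives about 8.3% at correlation 0.7, 7.0% at 0.9 and 6.5% at 0.95. The article gives no correlation, so these values are assumed.

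**The case against.** The strongest reply is that the article never says what per protocol means. A reader might infer that it compares workshop attenders with controls, but the documents do not support that as a fact. Women are invited and may decline, so a woman who stays away has arguably not departed from the protocol. The set could rest on enrolment counselling, on calls scheduled in the same months in both arms, or on completed follow-up. A condensed article may also leave the definition to the full protocol or analysis plan. All of this stands, and the missing definition alone is not the point here.

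A second reply is that the two bases answer different questions, and that the Discussion closes by describing the trial's purpose as evidence on effectiveness, the question given to intention to treat. That is a fair hint, but it is not a ranking. The Data analysis section still presents the per-protocol result as the efficacy answer, and nothing says which result governs. Equally, no passage says that success may be claimed on either, so the error rates above 5% for two tests are conditional.

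Three further readings go too far:

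- **That the bias must favour the intervention.** Attendance could also reflect the 20,000 UGX transport payment or greater difficulty in negotiating condom use.
- **That the intention-to-treat analysis uses completers only.** The article does not say so. It does plan to compare attrition rates and reasons by arm.
- **That per protocol should give way to a complier-average effect with arm as instrument and workshop attendance as exposure.** This requires arm to act only through attendance. All intervention women are due extra counselling at enrolment, and the calls do not depend on attendance. If those components raised uptake by 6 points, the workshop added nothing and half attended (assumed), the estimator would return 6/0.5 = 12 points, although the workshop effect is 0.

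**Conclusion.** The concern holds in a limited form. The article states that every analysis is run on both bases at one 5% level, ranks neither, and gives per protocol the efficacy label. This is stated text, not an omission. The label is not earned under the plausible definitions: each selects women after randomisation, by rules that would act differently in the two arms.

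The size is conditional. If the set depends on workshop attendance, selection alone could give an odds ratio of about 1.1 to 1.8. That range rests on the assumed attendance, selection strength and control rate; at high attendance and weak selection the distortion is small. Under call-completion or follow-up definitions the direction and size are unknown. The documents do not show that the per-protocol set is the workshop attenders, nor that the bias is certain to favour the intervention.

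**What to change.** In the Data analysis section, state that the intention-to-treat comparison of all enrolled women, by the allocation of the facility where they were recruited, is primary and alone carries the trial's conclusion. Keep per protocol as a supportive analysis with its criteria fixed before outcomes are seen, and remove the statement that it assesses efficacy.

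Because more loss is expected among controls, a sensitivity analysis of the intention-to-treat result that counts missing outcomes as non-use may be added. With more controls missing it would turn more controls into non-users, so it should be read as one assumption and not as a conservative bound. A complier-average analysis based on workshop attendance should not be used.

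The cost is a few sentences and a less prominent per-protocol result. No new data or change in sample size is needed.
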